### **Reporting of Adverse Events (AEs) or Unanticipated Problems involving Risk to Participants or Others**

The PI and study personnel will review any AEs that occurred during a participant's study experience and determine their cause and severity. AEs rated as grade two or higher on the scale below will be reported to the IRB within 7 days of the receipt by the Investigator when the report identifies a new risk or a change in the risk-potential benefits profile. In conjunction with the IRB, the PI then will determine if modifications to the protocol are warranted. At the end of each year that this study continues, an annual report of AEs will be collected and shared with the IRB.

#### **Grading of Severity of Adverse Events (AEs)**

0: No AE or within normal limits.

1: Mild AE.

2: Moderate AE.

3: Severe AE resulting in inpatient hospitalization, a persistent or significant disability/incapacity, or serious injury.

4: Life-threatening or disabling AE.

5: Fatal AE.

During weekly lab meeting, [name] will review data collection procedures with study staff and discuss any data collection problems which have been encountered. Quality control analyses will be conducted throughout the recruitment phase and will be discussed with study staff during lab meetings in an effort to quickly identify issues with data collection accuracy.

All subjects will be monitored by study staff throughout the study for any AEs or other safety issues. This study does not involve any known health risks. However, subjects may feel upset or uncomfortable by study procedures, such as the evaluation of clinical symptoms or the MRI scan. Subjects will be told that they may discontinue the experiment at any time they feel upset or uncomfortable. Study staff will immediately inform [name] of any subjects who becomes upset or withdraws themselves during the study, or experiences any adverse event.

If at some point during the study research staff may become concerned about a study participants' safety, they will follow the Crisis Assessment Procedures described below. Examples of concerning behavior include statements from the participant that life may not be worth living, that they would prefer to be dead, or that they have been having suicidal thoughts in the past month. These statements may occur in the context of the clinical or diagnostic interviews, but will also be monitored throughout the study visit by research staff, as they may occur unexpectedly. If such statements are made, a licensed mental health professional (the study PI, a licensed clinical psychologist, or licensed study staff) will assess risk as described below.

## **Crisis Assessment Procedures**

1. Express concern for subject. Point to specific behavior of concern:

*E.g. You said that you think a lot about killing yourself and this concerns me...*

*E.g. You said that you wish you were not living and this concerns me...*

2. Ask subject to speak with a licensed psychologist or psychiatrist

*E.g. I want to make sure you are safe. Would you talk with the study psychologist for a few minutes before you leave?*

a. If subject is willing, find study PI (a licensed psychologist) or a study collaborator who is a licensed psychiatrist or psychologist.

b. If a study PI or collaborator is not available, ask subject to walk to Psychiatric Assessment Services (1st floor of VPH) to talk to on-call doctor.

3. If the subject is willing to speak with the study PI or collaborator, a suicide screen will be conducted (Suicide Screen NIMH).

a. If the subject answers "yes" to any questions on the screen, a more thorough assessment will be conducted by the licensed professional (Suicide Risk Assessment C-SSRS), focused on the past month. If risk appears imminent, a discussion will be had with the subject about going to the Psychiatric Assessment Services (PAS). If the subject is unwilling to go voluntarily, VUPD [name] will be called to assist. If this occurs during an online study visit, then 911 will be called if the subject is unwilling to take safety measures (e.g. going to PAS themselves, calling their mental health provider).

b. If the subject answers "no" to all questions, the licensed professional will provide them with a list of resources (Mental Health Resources; Behavioral Safety Net) and discuss how they can maintain safety (E.g. I am still somewhat concerned about your safety, is there a family member you live with who may be able to keep an eye on you over the next few days? would you be willing to give your psychiatrist a call to let them know how you have been feeling?)

4. If subject is not willing to speak with study PI, ask subject if there is a family member who could pick them up from the appointment. Re-express concern for the subject's safety.

*E.g. I'm very sorry that the interview upset you. It may be difficult for you to concentrate on driving now. Is there a family member I could call to drive you home?*

- If subject has made directly threatening statements toward self or others, do not let subject leave-even if with family member. Tell family member that you are concerned for subject's safety and that they should talk to a doctor before they leave. If subject leaves anyway, call VUPD [name]

4. If subject refuses all offers (and has not made directly threatening statements or gestures):
- Walk subject out of building. If subject smokes, offer to sit with subject while they smoke and continue interview. If subject calms while smoking, repeat steps 2 and 3.
  - If subject does not smoke, offer to sit with subject in an open-air area and continue interview. If subject calms while outside, repeat steps 2 and 3.
  - If subject continues to refuse help, advise subject to call regular therapist or psychiatrist as soon as possible.
  - If subject has made directly threatening statements regarding self or others, note subject's vehicle and clothing. **Call VUPD [name]**

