## **6.0 RISKS**

---

The following procedures may have risks: clinical assessments, neuropsychological and cognitive testing, MRI scanning, psychotherapy intervention.

**Confidentiality:** The risk of confidentiality will be minimized by thorough training of all research personnel and the high level of security in our information systems. All subjects will be assigned a Subject ID numerical code to maintain anonymity of the participants and their test results. The Subject ID will serve as the primary identifying information on research data forms. Research personnel will comply with the ethical standards set forth by the IRB, NIH and the American Psychological Association. The records of this study, to include paper records and electronic records, will be kept private and secured in locked filing cabinets or in password-protected databases (RedCap) and folders (for videos). In any published report, we will not include any information that will make it possible to identify a subject.

If at any point during the study sessions the participant expresses any intent to harm themselves or others or a researcher becomes concerned for their safety, the researcher will contact the primary investigator or another licensed clinical psychologist on the research team. The clinical psychologist will conduct the brief ASQ suicide risk screen and the Columbia suicide severity scale for the past month. If the clinician is concerned for the participant's immediate safety they will continue with a safety plan and provide mental health resources and discuss alerting a family member or loved one of the concerns. If the participant cannot contract for safety and the clinical psychologist believes they may be a threat to themselves or others then the participant would be brought to the Psychiatric Assessment Services (PAS) for an evaluation for inpatient admission. If the study visit is occurring over zoom and an individual cannot contract for safety, the clinical psychologist will call 911 to the individual's address. Participants will be informed of this procedure during the informed consent process and again at the start of therapy.

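### The crisis steps do not carry the protocol's own rule on contacting a clinician into the branches for a participant who is unwilling to talk

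*Protocol*

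**What the plan says.** Three parts of section 6.0 of the protocol bear on this.

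- **Risks, Confidentiality paragraphs.** If a participant voices intent to harm, or a researcher is worried about safety, "the researcher will contact the primary investigator or another licensed clinical psychologist on the research team". A clinical psychologist then screens for suicide risk. The participant's willingness is not mentioned as a condition for the contact.
- **Grading of Severity of Adverse Events.** Staff with a safety concern are told that "they will follow the Crisis Assessment Procedures described below". The examples of concerning statements, the last of them limited to the preceding month, are "that life may not be worth living, that they would prefer to be dead, or that they have been having suicidal thoughts". After such statements, "a licensed mental health professional (the study PI, a licensed clinical psychologist, or licensed study staff) will assess risk as described below". The same section also carries a general duty, which begins "Study staff will immediately inform" and covers participants who become upset or withdraw. The recipient's name is removed from the public text.
- **Crisis Assessment Procedures.** Step 2a reads "If subject is willing, find study PI (a licensed psychologist) or a study collaborator who is a licensed psychiatrist or psychologist". If no such clinician is available, step 2b has staff "ask subject to walk to Psychiatric Assessment Services (1st floor of VPH) to talk to on-call doctor". Step 3, the suicide screen, applies to a participant willing to speak with the clinician. Two items are numbered 4. The first covers a participant unwilling to speak with the PI: staff ask about a relative who could collect them and repeat their concern. The second opens "If subject refuses all offers (and has not made directly threatening statements or gestures". Staff escort the participant outside, offer to stay, return to steps 2 and 3 if the participant calms, and otherwise advise a call to the participant's own therapist or psychiatrist. Steps 5 and 6 are note-taking and a prompt debrief of the PI.

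**The concern.** The general rule makes clinician contact a duty of staff. The numbered steps make it a consequence of the participant's consent to talk. Staff working from the steps under pressure could let a participant who has voiced suicidal thoughts leave without any licensed clinician having heard what was said or decided what to do.

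The population makes this matter. Section 1.0 states that persecutory delusions raise the risk of suicide and violence, and inclusion criterion 9 in section 3.0 requires every participant to have one. Suspicion of others is also a plausible reason to refuse a conversation with an unfamiliar clinician; that is my inference and not a statement in the protocol.

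This is a participant-safety point. It has no bearing on sample size, power or type I error.

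**Working it through.** No arithmetic applies. The check sets the general duty beside each route through the Crisis Assessment Procedures and asks whether a clinician is contacted before the participant leaves.

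| Route | Clinician contact named in the steps | Depends on agreement? | Placed before departure? |
|---|---|---|---|
| Step 2a | PI or licensed collaborator is fetched | Yes | Yes |
| Step 2b | Participant is asked to go to Psychiatric Assessment Services (PAS) | Yes | Yes |
| Step 3, 3a, 3b | Screen, and fuller assessment if positive | Yes | Yes |
| First step 4, no direct threat | None | – | – |
| Second step 4 | None, unless the participant calms and steps 2 and 3 are repeated | Yes | Only if they calm and agree |
| Step 6 | Debrief of the PI | No | No time set relative to departure |

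1. **The trigger is the same.** Section 6.0 Risks and the Grading section both start from concern for a participant's safety. One says to contact a clinician; the other sends staff to the steps.

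2. **The promised assessment can drop out.** The Grading section says a licensed professional will assess risk by the procedure that follows. For someone who will not talk, that procedure contains no assessment.

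3. **The first step 4 has the same gap as the second.** A participant who declines the PI but accepts a lift from a relative leaves with no listed call to a clinician. A direct threat changes this: staff are then told not to let the person go, to tell the relative that a doctor should be seen first, and to call campus police (VUPD) if the person leaves anyway. Below that threshold no clinician is named.

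4. **The threshold sits above the protocol's own examples.** The Grading section gives three kinds of statement: life may not be worth living, a preference to be dead, and recent suicidal thoughts. None of the three is worded as a direct threat. A refusing participant who says only one of them can fall in either branch.

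5. **Escalation without consent exists but is not reached.** Under step 3a, a participant at imminent risk who will not go to PAS can be met by VUPD. That follows a clinician's assessment, which the steps reach only if the participant first agrees to talk.

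6. **The general duties still stand.** Nothing in the steps cancels or postpones the contact required under Risks or the duty to inform in the Grading section. Neither duty appears in the steps or is tied to departure.

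**The case against.** The strongest reply is that the contact is already required. The rule under Risks applies throughout study sessions, arises as soon as staff are concerned, and so precedes either step 4. The duty to inform is immediate, and a participant who refuses every offer may well count as upset. On this view the steps make only the conversation conditional, because a volunteer cannot be made to talk, and leave staff notification untouched. Exposure is also limited: section 6.0 says therapists have at least three years of experience with psychotic disorders and are supervised by the PI, and licensed study staff may assess risk themselves. The second step 4 keeps staff with the participant and tries again.

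Much of this stands. A reader might infer that the protocol provides no clinician contact for a refusing participant, or that two instructions conflict outright. The documents support neither: the general rule is unconditional, and the steps are silent on it without overriding it.

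A reader might also infer that the Critical Risk Factors list has no function because no step refers to it. That cannot be settled from text taken from a PDF, since the list may be a call-out whose layout was lost, and a voiced specific plan may already count as a direct threat.

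What the reply does not remove is that staff are told to follow the steps, and the steps omit the contact where the participant is least likely to be seen by anyone else. Visits run by unlicensed research staff are where this matters most.

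**Conclusion.** The point holds as a failure to carry an existing safeguard into the stepwise procedure. In both items numbered 4, an unwilling participant without a direct threat can leave with no clinician contact named in the steps, and the only contact with the PI that does not need agreement is a debrief with no time tied to departure.

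The size cannot be expressed as a rate. The protocol gives no frequency of safety concerns or of refusals, and a count of steps would not measure risk. The conclusion rests on two assumptions: that staff in a crisis work mainly from the numbered list, and that statements like the Grading section's examples are not treated as direct threats. If the team routinely applies the rule under Risks as well, the practical gap is small.

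The change should be made, because it is cheap and puts into effect what the protocol already intends.

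**What to change.** At the start of the first step 4 in the Crisis Assessment Procedures, so that it governs both branches, add:

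> If the participant is unwilling to speak with a clinician, staff phone the PI or another licensed psychologist on the team (the PAS on-call doctor if neither is reachable) before the participant leaves, report what was said and any critical risk factor, and follow that clinician's decision. If the participant leaves first, the call is made at once.

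Keep step 6 as the follow-up debrief. The critical risk factors then inform the clinician's decision and do not create an automatic hold.

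Optionally, reword the bullet on direct threats at the end of the second step 4. That branch excludes such threats at entry, so the bullet would be clearer if it applied to a threat made at any point during the steps.

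The cost is a wording amendment through the IRB and a staff briefing, then one phone call and a short delay when a participant is unwilling to speak with a clinician.

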### **CRITICAL RISK FACTORS**

- subject has a specific plan or has implied a plan
- subject has access or has implied access to weapon
- recent attempt or history of attempts
- subject dwells on death or has strong suicidal ideation

5. Make thorough notes describing concerning behavior, help offered, and subject's responses. Place in subject file.

6. Debrief study PI as soon as possible. PI will notify the IRB within 7 days if AE is found to be a 2 or higher on the scale above.

### **7.0 Study Withdrawal/Discontinuation**

---

Subjects may elect to withdraw from the study at any point. If this occurs due to adverse effects, immediate treatment will be provided. Subjects may be discontinued by the investigator for a number of reasons. These include the following:

1. mental fatigue or anxiety to the point that it is interfering with their ability to complete the study
2. significant distress during the structured, manualized therapy sessions, such that the therapy does not appear clinically appropriate. Withdrawal will not affect any future clinical care at Vanderbilt University Medical Center.
3. Subjects who have adverse events of moderate severity or greater who, in the judgment of the principal investigator, may be unable to complete the study or whose health may be compromised by further participation.

### **8.0 Statistical Considerations**

---

Given that this is a clinical trial, following randomization, all participants who completed the baseline assessment and were randomized will be included in an intent-to-treat analysis, to capture as much data as possible. Regarding the primary aims, **AIM1**: linear regression will be used to test if the severity of persecutory delusions is associated with volatility at baseline, and whether change in delusion severity over 8-weeks is associated with change in volatility across all psychosis participants. These changes are expected to be stronger in the WIT group than in those receiving Befriending. **Aim 2**: Neurobiological underpinnings of volatility will be assessed pre/post treatment in psychotic disorder patients using task-based fMRI. It is hypothesized that activation in the ventral striatum, insula and dlPFC will covary with volatility during a belief updating task. Persecutory delusion severity is expected to be positively associated with volatility-related task activation. Patients receiving WIT are expected to demonstrate normalization (i.e. reduced) activation in these regions post-treatment, which will be associated with delusion severity, representing neurobiological targets for future treatment trials.

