**In the proposed study, we aim to examine the impact of a previously established psychotherapeutic intervention for persecutory delusions on computational parameters of belief updating (e.g. volatility) and associated brain activation in individuals with psychotic disorders.** Identifying whether belief updating ability changes in response to a therapeutic intervention would advance our understanding of delusions in the following ways: 1) determine whether changes in persecutory delusion severity are associated with changes in belief updating ability, clarifying mechanistic models of delusions; 2) identify neurobiological correlates of changes in persecutory delusion severity, providing future neurobiological targets for intervention; and 3) begin to examine whether psychotherapy is a mechanism-of-change for belief updating ability and persecutory delusions (i.e. whether changes in belief updating parameters mediate the relationship between treatment and change in delusion severity).

We propose an RCT in which individuals randomized to receive either WIT or Befriending therapy, an active control psychotherapy focused on the individual's interests. Inclusion of an active control group will extend previous findings against TAU and begin to address whether cognitive-behavioral interventions (versus the general factors of therapy) impact belief updating. We will recruit approximately 150 participants to enroll 60 adults (18-65 years) with a non-affective psychotic disorder (i.e. schizophrenia-spectrum disorder, delusional disorder). Participants will be randomly assigned to either the WIT (n=30) or Befriending (n=30) groups. The treatment lasts for 8 weeks. Both groups will be asked to complete an fMRI scan at baseline and end of treatment, as well as mid-treatment cognitive and clinical assessments and assessments at 24-week follow-up.

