### **5.9 Mid-Treatment Assessment**

In the middle of treatment (Week 4) study participants will be asked to complete a brief, 2-3 hour assessment. This assessment will include clinical interview, self-reports, and the 3PRL task (described above).

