### **5.10 End of Treatment Assessment**

At the end of treatment (Week 8), all assessments (except the diagnostic interview and childhood trauma questionnaire), as well as the MRI, will be repeated.

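### Section 8.0 promises an intent-to-treat analysis of everyone randomised, but the Aim 1 regression on 8-week change can by itself use only participants seen at week 8

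*Protocol*

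**What the plan says.** Section 8.0 sets the analysis population: "all participants who completed the baseline assessment and were randomized will be included in an intent-to-treat analysis, to capture as much data as possible". It then gives the Aim 1 method in two parts. At baseline, "linear regression will be used to test if the severity of persecutory delusions is associated with volatility at baseline". Over time, the same regression tests "whether change in delusion severity over 8-weeks is associated with change in volatility across all psychosis participants". One sentence on the arms follows: "These changes are expected to be stronger in the WIT group than in those receiving Befriending". No model is attached to that expectation.

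The planned size is in Section 2.0: "Participants will be randomly assigned to either the WIT (n=30) or Befriending (n=30) groups". Outcomes are collected at baseline, week 4, week 8 and week 24. Week 4 includes a clinical interview, questionnaires and the reversal-learning (3PRL) task (Section 5.9). Section 5.10 covers the endpoint visit: "At the end of treatment (Week 8), all assessments" are repeated with the scan, apart from two instruments.

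Loss to follow-up is foreseen. Section 7.0 says "Subjects may elect to withdraw from the study at any point" and also allows the investigator to discontinue a participant, for instance for marked distress in therapy. It does not say whether assessments continue afterwards. No expected dropout rate is given.

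**The concern.** The protocol fixes both a population and a model, and the two do not fit. A baseline-to-week-8 change needs a week-8 value. A participant who leaves before then has no value for the dependent variable, so ordinary linear regression omits that person. The section states nothing that would bring such participants back, and the week-4 data do not enter the stated Aim 1 analysis. This sits badly with the aim of capturing as much data as possible.

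Two things are at stake. In a trial of 60, each lost participant costs precision. If the arms are also compared on change, loss that relates to early response and differs by arm can distort the comparison. The protocol gives some reason to expect a difference: Section 6.0 notes that the WIT material may upset some participants, whereas Befriending keeps to neutral topics.

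**Working it through.** **Inputs from the protocol.** 30 + 30 = 60 randomised. Alpha, power, effect size and dropout are not stated, so nothing beyond this sum can be reproduced.

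**Assumptions.** Loss before week 8 of 0 to 40%; two-sided alpha 0.05; 80% power.

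**Step 1: participants used and precision of the pooled association.** Number analysed: N = 60 × (1 − d). Detectable correlation by Fisher's z: r = tanh[(1.960 + 0.842)/√(N − 3)]. For N = 60, 2.802/√57 = 0.371 and r = 0.355. For N = 36, 2.802/√33 = 0.488 and r = 0.452. The last column is power for a true correlation of 0.354, roughly what 60 participants can detect.

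| Assumed loss | N used | Detectable r | Power at r = 0.354 |
|---|---|---|---|
| 0% | 60 | 0.355 | 80% |
| 10% | 54 | 0.373 | 75% |
| 20% | 48 | 0.395 | 70% |
| 30% | 42 | 0.421 | 64% |
| 40% | 36 | 0.452 | 57% |

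**Step 2: bias in the pooled association.** Simulation with assumed correlations of 0.6 (baseline, week 4), 0.5 (baseline, week 8) and 0.7 (week 4, week 8), and no true arm difference. In WIT 25% are lost, with dropout depending on worsening by week 4; in Befriending 10% are lost at random. The expected number remaining is 30 × 0.75 + 30 × 0.90 = 49.5 of 60. With a log-odds slope of dropout on worsening of 1.5, the completer and full-data slopes were 0.195 against 0.201, 0.292 against 0.300, and 0.489 against 0.500, for assumed correlations between the two changes of 0.2, 0.3 and 0.5. That is 2 to 3% towards zero. Over log-odds slopes from 0.5 to 3, it is about 1 to 5%.

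**Step 3: bias in the difference in mean change between arms, completers only.** Same correlations, no true difference; bias is in SD units towards WIT.

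| Dropout assumed | Bias |
|---|---|
| Equal rates and mechanism in both arms | 0.00 |
| 20%/15%, worsening-related in both arms, slope 1 | 0.03 |
| 25%/10%, worsening-related in WIT only, slope 0.5 | 0.07 |
| same, slope 1 | 0.13 |
| same, slope 1.5 | 0.175 |
| same, slope 2 | 0.20 |
| same, slope 3 | 0.24 |

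In the five 25%/10% rows, adjusting completers for baseline alone left 0.05 to 0.16 SD. An estimator using baseline and week 4 had bias of about 0.00. That last result follows from the set-up, because dropout was made to depend only on baseline and week-4 values.

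A milder case has a true difference of −0.50 SD, about 17% missing, and WIT dropout depending on the week-4 level. Completers gave −0.517 (empirical SE 0.285); the estimator using week 4 gave −0.502 (SE 0.275).

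**The case against.** **The text never prescribes a complete-case analysis.** Regression after multiple imputation would satisfy both sentences, and missing-data handling often belongs in an SAP, which is not at hand. A reader might infer that the plan has chosen to drop participants; the protocol does not say so. What stands is narrower: it states a population and a model, and the model as written does not reach the population.

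**The stated regression is a pooled association.** A reader might take the 0.07 to 0.24 SD as bias in the planned Aim 1 result. It is not, because that regression has no arm term and its slope is barely affected in Step 2. The figures apply to a difference between arms that Section 8.0 expects but does not model. For the same reason, the usual efficiency argument for baseline adjustment over change scores does not count here, since it concerns an arm contrast. This objection stands in full.

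**The week-4 data have limits.** Section 5.9 does not name the PSYRATS, so a week-4 delusion rating is likely but not explicit. The Amendment History (Amendment 6) says the week-4 and week-24 3PRL runs through an external university server, whereas Section 5.6 describes an in-scanner version at baseline and week 8. Week-4 volatility may therefore not be interchangeable with the other two. Week 4 also adds nothing for participants lost before it. These points shape the fix but do not remove the mismatch.

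**Conclusion.** The concern holds in limited form. The population and the longitudinal Aim 1 model in Section 8.0 do not match; the baseline regression is not touched. For the pooled association, the sure consequence of any loss is fewer participants: 54 to 36 of 60 at 10 to 40% loss, with the detectable correlation rising from 0.355 to between 0.373 and 0.452. Bias there is small under the dropout pattern examined. For a WIT-versus-Befriending difference in change, completer bias runs from about 0 to 0.24 SD. The upper part of that range needs both unequal loss and dropout driven by worsening in one arm only. The documents do not show that this will happen. Apart from 30 + 30 = 60, every figure rests on assumed dropout, correlations, alpha and power.

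**What to change.** Revise Section 8.0 so that the stated population can be analysed:

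- **Association.** Keep the question. Estimate it on all randomised participants by multiple imputation that includes arm, baseline and week-4 values, or by a bivariate mixed model.
- **Arm difference in change.** Name a model: a repeated-measures mixed model using baseline, week 4 and week 8, with arm, visit and their interaction, reading the week-8 contrast.
- **Sensitivity.** Add one analysis for data not missing at random, such as a delta shift applied to missing WIT outcomes.
- **Week 4.** Confirm that the PSYRATS is rated at that visit. Allow for the different 3PRL administration, for example by using week-4 volatility only as an auxiliary variable in the imputation.

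If this is not adopted, describe the change regression as a completer analysis and confine the intent-to-treat statement to analyses that can meet it.

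The cost is protocol or SAP wording and some extra analysis, with no new visits or data. The main methods then rest on a missing-at-random assumption, which is why the sensitivity analysis is needed.
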